## Summary

**Introduction:** It is estimated that 90% of hospitalized adult patients require a vascular access device compatible with a peripheral venous network. The adoption of good indication, insertion and maintenance practices contributes to the reduction of complications, and consequently a longer time of permanence of the devices free of events. Midline catheters (called *midline*) recently arrived in Brazil have stood out in the last decade as devices that have fewer complications and greater durability. However, the costs associated with the technology restrict its incorporation, especially in public institutions. It is not to our knowledge that midline catheters have been compared with devices for the same purpose in hospitalized patients.

**Objective:** To compare the use of the midline catheter for the *length of stay free of complications with the use of a long peripheral intravenous catheter during continuous or intermittent intravenous therapy in adult clinical patients hospitalized for up to 30 days.*

**Method:** Randomized clinical trial followed by an economic analysis. The study will be developed with adult patients admitted to clinical units of a public university hospital who have difficult venous access, where the intervention group will receive the insertion of a PowerGlide Pro™ Midline catheter, and the control group the insertion of an Introcan Safety Deep Access long peripheral intravenous catheter. The primary outcome will be the length of stay of the vascular access free of complications (infiltration, phlebitis, occlusion, accidental removal, catheter-associated bloodstream infection, and deep vein thrombosis). **Expected results:** To demonstrate evidence in the reduction of events and longer length of stay related to the use of the *midline catheter* and the costs to the health system. Based on the results, we propose the incorporation of the *midline catheter for* continuous and intermittent intravenous therapy for up to 30 days in the public health system.

## 1. INTRODUCTION

The use of intravenous devices is one of the most common invasive procedures among hospitalized patients, with the main purpose of administering medications, fluids, blood products, and nutritional support. In the United States, it is estimated that approximately 150 million peripheral venous catheters and 5 million central venous catheters (CVCs) are inserted annually. Peripheral intravenous catheters are also the most commonly used devices in our practice, according to an observational point-prevalence study conducted in March 2022 at HCPA. On this occasion, a total of 746 venous access devices were found in hospitalized patients, with a predominance of peripheral venous catheters, with a total of 672 accesses evaluated.

In recent years, good practices related to peripheral venous catheters have been disseminated by new international consensus and *guidelines*. Among these, skin antisepsis with 2% chlorhexidine, before the insertion of any peripheral venous access device, implementation of *bunddles* in which teams of specialized nurses perform the indication, insertion and maintenance of catheters, the use of ultrasound (US) to evaluate the venous network and catheter insertion, application of evidence to select the catheter insertion site preferably in the veins of the upper forearm (cephalic vein), The use of longer catheters with optimized caliber, the use of appropriate fixation dressings, and the use of anti-reflux connectors can reduce or eliminate intravenous complications and help prolong the use of these devices.

In addition to these good practices, the introduction of new technologies has made peripheral venous catheters more complex, due to their manufacturing material, new design and new protection strategies for the insertor, making these catheters less prone to complications and with greater safety and durability.

Long and midline *peripheral catheters* are also indicated for infusion of peripherally compatible solutions, i.e., pH 5-9, drugs with osmolarities <600 mOsm/L, any drug or solution not associated with potential endothelial damage, history of difficult venous access, obesity, vasculopathic and/or hypovolemic diseases. In addition to the indications, these devices should be inserted by trained nurses under ultrasound guidance for cannulation of deeper veins, making the insertion technique more accurate, more successful and with less risk of complications.

Regarding the proposed therapy time and catheter permanence, international guidelines indicate the use of these catheters for peripherally compatible treatments of five to 14 days, with a permanence time of no more than 30 days. In a study with 255 patients, Bahl et al,

(2019) demonstrated that the long peripheral venous catheter had a mean length of stay of five and a half days. In a systematic review with data from 18,972 *midline* catheters, the mean length of stay was 16.3 days. In a recent retrospective cohort study in which the length of stay of long catheters was compared with midline catheters, *involving 184 patients with acute cardiovascular disease, the mean length of stay of the catheters was 14.0 days (IQR: 7.0-25.0), and the midline catheter reached 54 days of stay*.

The benefit of using a longer catheter is that it allows at least two-thirds of the catheter to reside in the vein, making it less likely to cause chemical phlebitis and infiltration. Even if the indications for the use of these devices are met, adverse events and complications may occur during their use, such as catheter-associated bloodstream infection (ACSC), venous thrombosis, occlusion, phlebitis, infiltration, and accidental removal.

In a multicenter cohort study including 5,105 *midline* and 5,758 *peripherally inserted central catheter (PICC)*, ACSC rates of 0.4% and 1.6% (midline and PICC) and occlusion rates of 2.1% and 7.0% (midline and PICC) were observed, concluding a lower risk of complications for patients using midline. Also with reference to *the midline*, the systematic review by Tripathi et al, 2021, showed that 64% of the studies did not report any catheter-related infection, with a venous thrombosis rate of 4.1%, occlusion rate of 3.8%, phlebitis 3.4%, and infiltration of 1.9%.

Driven by the technological advancement that has made several catheters available for clinical practice, nurses have been at the forefront of decision-making for the best device, and should consider the patient's venous network, the characteristics of the proposed infusional therapy, and the availability and cost of the material in their institution at the time of choice.

Thus, the advancement of technology has instigated a discussion about the best way to incorporate new medical-hospital products that bring benefits to patients, but are expensive for adoption by public health institutions. The public and private sectors are developing initiatives to improve the entry of these products, but most of the time they come up against the specific analysis of the unit value, leaving something to be desired in terms of an in-depth and evidence-based evaluation.

At the Hospital de Clínicas de Porto Alegre, since 2018, nurses from the Vascular Access Program have worked directly in the indication, insertion, maintenance, and monitoring of venous access devices available for care practice, also participating in the evaluation and issuance of opinions on new venous catheters in order to incorporate these new technologies.

In Brazil, as of 2006, the Ministry of Health (MS) defined the policy for the incorporation of new technologies within the scope of the Unified Health System (SUS),

advocating a complete economic evaluation as a fundamental item for the analysis of the incorporation of new technologies. In 2012, the Methodological Guideline for Economic Assessment of Health Technologies was published, and these initiatives are in line with the current National Policy for Health Technology Management, whose objective is to maximize the health benefits to be obtained with the available resources, ensuring the population's access to effective and safe technologies, in conditions of equity.

Economic evaluations of health technologies are always comparative and should be based on the assumption that the technology evaluated is at least as effective as the existing or available options in the system. Thus, it can be concluded that data from economic evaluation studies are an indispensable resource to support decision-making on the incorporation of new technologies in health.

In view of the above and the gap regarding the cost, safety and results of the use of midline catheters in university hospitals in Brazil, we propose this randomized clinical trial followed by an economic analysis of microcosting of the use of midline catheter versus long peripheral venous catheter in adult patients admitted to a public university hospital.

The hypothesis to be tested is that the use of the *midline* catheter has a longer permanence time free of complications that lead to the removal or replacement of the vascular access (infiltration, phlebitis, occlusion, accidental removal, infection and deep vein thrombosis) compared to the long peripheral venous catheter when routinely used during continuous or intermittent intravenous therapy in hospitalized adult clinical patients. This study is relevant because, in addition to testing this hypothesis, the authors will also evaluate the economic impact of incorporating the technology into a public health institution.

## **2. GOAL**

### **2.1 General objective**

Compare the use of the midline catheter (*midline*) regarding the length of stay free of complications with the use of a long peripheral intravenous catheter during continuous or intermittent intravenous therapy in adult clinical patients hospitalized for up to 30 days.

### **2.2 Specific objectives**

- Analyze the indicators of good practice:

- a) Time of permanence of the venous access device free of complications: (infiltration, phlebitis, occlusion, accidental removal, catheter-associated bloodstream infection and deep vein thrombosis);
  - b) Rates of bloodstream infections associated with the type of catheter used;
  - c) Occurrence of deep vein thrombosis associated with the type of catheter;
  - d) Success rate in the first puncture attempt related to the type of catheter;
- Perform the economic analysis of the incorporation of the technology – midline catheter:
- a) Comparison of the cost of the two technologies used, type of catheter;
  - b) Costs of treatment of isolated or combined complications and catheter replacements resulting from associated infections;
  - c) Cost of avoided complications;

### **3. METHOD**

#### **3.1 Design**

This is a randomized, parallel, open-label, controlled, single-center clinical trial, blinded to statistical analyses. In clinical trials, the investigator applies an intervention and observes its effects on outcomes. The main advantage of a clinical trial over an observational study is its ability to demonstrate causality. This study will be registered on the Platform *Clinical Trials* and will strictly follow the guidelines of the *Consolidated Standards of Reporting Trials* (CONSORT).

The economic evaluation will be based on micro-costing where all cost components are defined at the most detailed level from individual patient treatment data, such as from the medical record review. The unit of analysis in micro-costing is the individual service.

Considering the perspective of the public health system, the method seeks to assess costs as accurately as possible, including the direct and indirect costs of patient care. The time horizon considered will be 30 days. Bottom-up micro-costing will be carried out, as this is considered the gold standard for economic evaluations in health, considering that the collection of individual data enables a higher level of precision in the estimation of costs.

### 3.2 Location, Population, and Study Period

HCPA is a public and university institution, of a general nature, linked to the Unified Health System (SUS), part of the network of hospitals of the Ministry of Education (MEC) and academically connected to the Federal University of Rio Grande do Sul (UFRGS). As a public and university hospital, side by side with care, HCPA promotes teaching and research in health. All these actions are developed in an integrated manner and focused on the transformation of realities, contributing, on different fronts, to the quality of life of the population, the improvement of the public health network and the evolution of knowledge in the area .

The HCPA has 836 beds, divided into: Clinical/Surgical Inpatient Units (435), Research Inpatient Unit (6), Obstetric **Inpatient Unit (44)**, Pediatric Inpatient Unit (88), Neonatal Inpatient Unit (30), **Adult Psychiatric (46)**, **Childhood/Adolescent Psychiatric (7 )**, Adult Intensive Care Units and Coronary Care Unit (72), Emergency Intensive Care Unit (10), Paediatric Intensive Care Unit (13), Neonatal Intensive Care Unit (20), Emergency (46), Paediatric Emergency (13) and **Obstetric Emergency (6)**. In 2021, there were a total of 28,780 hospitalizations, with an average bed occupancy rate of 76.6%, with an average length of stay of 8.6 days.

The study population will consist of adult clinical patients who require continuous or intermittent intravenous therapy for more than five days and with a proposed end of up to 30 days, hospitalized in the clinical units of the HCPA, with no indication of continuity of treatment in an outpatient setting.

The study will be conducted in five inpatient units, with a total of 181 beds located between the fourth and seventh floors of the hospital, in the south and north wings. The inpatient units in the south wing have private or double accommodation rooms with capacity for up to 34 patients, preferably adults, who are cared for by up to two nurses in each shift and technical nursing staff in a defined quantity according to the specific demand of the place. The units in the north wing have three-bed wards with capacity for up to 45 adult patients, who are cared

for by up to three nurses in each shift and a technical nursing team in a quantity defined based on the specific demand of the unit.

The study period will be from October 01, 2022 to March 31, 2023. The inclusions will be carried out from Mondays to Fridays, according to the study protocol.

### **3.3 Inclusion and exclusion criteria**

a) Inclusion: Patients aged 18 years or older, after 24 hours of admission to the inpatient unit, indication of continuous or intermittent intravenous therapy during hospitalization for more than five days and who have a definition of difficult intravenous access (DIVA ), characterized by the occurrence of two or more failed attempts at peripheral venous access using the traditional technique, with no visible and palpable veins or a patient with a declared or documented history of difficult venous access.

b) Exclusion: patients requiring continuous or intermittent intravenous therapy during hospitalization for more than five days, with the presence of stage IIIB chronic renal failure with ECD <45, due to the potential need for venous arteriosus fistula in the upper limb; patients who are in COVID-19 care beds, due to the need for specific attire and time spent; who are suspected of having sepsis according to institutional protocol, who have a critical or unstable clinical condition defined by the criteria for the care of complications for adult patients at the HCPA: Airway: respiratory dysfunction requiring intubation; Respiration: respiratory rate less than 8 and greater than 35 respiratory movements per minute and/or oxygen saturation less than 90%; Circulation: heart rate less than 40 or greater than 140 beats per minute, systolic blood pressure less than 80 mmHg, systolic blood pressure between 80 and 90 mmHg, and worsening of the clinical picture; State of consciousness: decreased Glasgow Coma Scale greater than 02 points, prolonged (greater than 5 minutes) or repeated seizure; Suspicion of sepsis or a patient with cognitive impairment (as described in the patient's medical record based on medical evaluation) at the time of selection; difficulties in understanding the Informed Consent Form (ICF) (APPENDIX A) and without a family member or guardian to consent to entry into the study;

### **3.4 Sample estimation**

Considering a study that verified the efficacy of midline catheters compared with a strategy of using conventional catheters (peripheral venous catheter and central venous catheter) for patients requiring intravenous therapy for more than five days, the sample size

was calculated to detect differences of five days between the days free of complications between the intervention group (use of midline catheter) and the control group (use of a long peripheral intravenous catheter), using the online version of the PSS Health tool.

Considering a power of 90%, a significance level of 5%, and a standard deviation of seven days, as found in a pilot study conducted at HCPA in 2021, the total sample size of 84 subjects was reached. Adding 20% for possible losses, the sample size should be 102 subjects (51 in each group).

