**Figure 01. Summary flowchart of the study protocol**

### **3.10 Data analysis**

The data will be entered into the REDCap database and extracted for analysis in the *Statistical Package for the Social Sciences - SPSS v.21*. Continuous variables will be described as mean and standard deviation for those with normal or median distribution and interquartile range for asymmetric variables. The *Kolmogorov-Smirnov and Shapiro Wilk* tests will be used to test the normality between the quantitative variables. Categorical variables will be expressed as percentages and relative frequencies. Quantitative variables will be compared using Student's t-test or Mann-Whitney test according to data distribution. The associations of the clinical characteristics of the patients will be performed using Pearson's chi-square test. The groups will be compared in relation to complication-free survival by *Cox analysis* and *long-rank* test. A  $P < 0.05$  will be considered statistically significant.

The analysis regarding microcosting will occur through a decision tree model in which hospitalized adult patients can be allocated to the use of a *Midline catheter* or a long peripheral venous catheter.

These patients will be subject to the occurrence of composite outcomes such as infiltration, phlebitis, occlusion, accidental removal, catheter-associated bloodstream infection, and deep vein thrombosis. The economic outcomes will be the costs of using the *Midline Catheter and the Long Peripheral Intravenous Catheter* and the resolutions of infiltrations/extravasation, phlebitis, occlusions, catheter-associated bloodstream infection, and deep vein thrombosis. The values will be expressed in reais and the analysis will be performed between the absolute and percentage difference between the number of composite outcomes and cost between the two groups studied (*Midline catheter* and long peripheral intravenous catheter).

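### The 90% power in section 3.4 belongs to a comparison of fully observed mean days and is unsupported for the planned log-rank/Cox analysis of censored complication-free survival

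*Protocol*

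**What the plan says.** Section 3.4 states that the sample size "was calculated to detect differences of five days between the days free of complications between the intervention group" and the control group. Its inputs read "Considering a power of 90%, a significance level of 5%, and a standard deviation of seven days", the SD coming from a local pilot study in 2021, and it reports that "the total sample size of 84 subjects was reached". It continues: "Adding 20% for possible losses, the sample size should be 102 subjects (51 in each group"). The section names no test, hazard ratio, control-arm mean or median, event proportion or event count.

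The primary outcome (Summary and section 3.6.1) is how long the access lasts without infiltration, phlebitis, occlusion, accidental removal, bloodstream infection or deep vein thrombosis. Under section 3.8 each patient is followed until the catheter is removed or replaced, or until discharge, death or day 30, whichever is first.

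Section 3.10 states: "The groups will be compared in relation to complication-free survival by" Cox analysis and the log-rank test. It also lists Student's t-test or Mann-Whitney for quantitative variables in general, without tying either to the primary outcome.

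**The concern.** A catheter taken out because therapy has ended, or because the patient goes home, has not had a complication, so its complication-free time is censored. A calculation on mean days treats each patient's time as a complete measurement. The log-rank test draws its information from the complications observed, so the two calculations need not agree, and nothing in the protocol connects them.

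Section 3.11 links the result to possible adoption of the midline catheter in the public health system. If the trial finds no significant difference, readers will weigh that result by the stated 90%. They need to know which analysis the figure describes and what event count the planned analysis would require.

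**Working it through.** **1. Reproduce the protocol's figure.** Inputs from section 3.4: difference 5 days, SD 7 days, power 90%, alpha 5%. Sidedness is not stated.

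- Per arm, n = 2 × (1.960 + 1.2816)² × (7/5)² = 2 × 10.507 × 1.96 = 41.2, rounded up to 42, so 84 in total.
- The exact t-test needs 42.2 per arm, and its power at 42 per arm is 89.9%.
- A one-sided test would give 68, so the calculation is two-sided.

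The 84 is thus a comparison of means. No term in it represents censoring or an event count.

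**2. The planned analysis, with labelled assumptions.** The protocol gives no hazard ratio (HR), so one must be assumed. With exponential times, HR = control mean / (control mean + 5). One candidate control mean is the 5.5 days that section 1 cites for long peripheral catheters. That figure is catheter stay in a background study, so using it as time to complication is itself an assumption.

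- HR = 5.5/10.5 = 0.524, and ln HR = −0.6466.
- Events for 90% power (Schoenfeld) = 4 × 10.507 / 0.6466² = 100.5, so 101. Freedman's formula gives 108.
- Power with D events = Φ(√D × 0.6466/2 − 1.960). For D = 84 this is Φ(2.963 − 1.960) = 84%.

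The same formulas across control means and event proportions, for 84 patients:

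| Control vs midline mean (days) | HR | Events for 90% | Power, 100% with event | 80% | 60% | 40% |
|---|---|---|---|---|---|---|
| 5.5 vs 10.5 | 0.524 | 101 | 84% | 76% | 63% | 47% |
| 7 vs 12 | 0.583 | 145 | 70% | 60% | 48% | 35% |
| 9 vs 14 | 0.643 | 216 | 53% | 44% | 35% | 25% |
| 14 vs 19 | 0.737 | 451 | 29% | 24% | 19% | 14% |

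The HR detectable with 90% power is exp(−2 × 3.2415/√D). That is 0.49 with 84 events, 0.40 with 50 and 0.33 with 34.

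**3. Is 84 the right ceiling?** A patient lost after insertion still contributes time and possibly an event to a log-rank test, so up to 102 patients could count. At HR 0.524, 102 events give Φ(√102 × 0.6466/2 − 1.960) = Φ(1.305) = 90%. That would require 101 of 102 patients (99%) to have a complication. With 80% of 102 (81.6 events) power is 83%, and with 60% (61.2 events) it is 72%.

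**4. Keep the protocol's SD.** Exponential times at 5.5 and 10.5 days imply a pooled SD of √((5.5² + 10.5²)/2) = 8.4 days, not 7. Log-rank simulations at 42 per arm used Weibull times with SD 7 in each arm, cut at day 30. Therapy either did not stop early or ended at five days plus an exponential time of mean 3, 5 or 10 days. Approximate power:

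- 5.5 vs 10.5 days: 87–98%
- 7 vs 12 days: 81–96%
- 9 vs 14 days: 79–91%
- 14 vs 19 days: 55–80%

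Under a different pattern, exponential censoring of mean 7 to 30 days from insertion or none, the figures were 87–95% at 5.5 vs 10.5, 73–80% at 9 vs 14 and 41–80% at 14 vs 19. At 5.5 vs 10.5 days power rises with censoring because the hazards differ most early, so censoring removes the less informative late period. Those hazards are not proportional.

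**5. Loss allowance.** 84 × 1.2 = 100.8, made up to 51 per arm, gives 102. A 20% loss from 102 leaves 81.6, whereas keeping 84 after a 20% loss needs 84/0.8 = 105. The loss that 102 covers is 1 − 84/102 = 17.6%. Power of the means calculation at 41 per arm is 89.2%.

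**The case against.** The strongest reply is that a shortfall has not been shown. A reader might infer that 84 evaluable patients cannot deliver 90% in the planned analysis. The documents do not support that as a fact: the exponential examples replace the protocol's SD of 7 with a larger one, and with SD 7 kept and short control times the log-rank test reaches 90% or more. This part of the reply stands.

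Four related inferences also go too far:

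- The hospital stay in section 3.2 ("with an average length of stay of 8.6 days") cannot be used to measure censoring. It is a hospital-wide average, while trial patients enter after 24 hours on the unit and need more than five days of therapy.
- Section 3.4 says that it considered a trial against conventional catheters. It does not say that the five days is that trial's result, so the effect cannot be called borrowed from the wrong comparator.
- The pilot behind the SD is not described. If it recorded observed days in place, some truncation may already be in the 7 days. That still gives no event count for a log-rank test.
- The loss allowance does what its wording says, since 20% was added. The gap is about two patients and less than one percentage point of power.

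It could also be said that section 3.10 lists a t-test, which would match the calculation. That sentence covers quantitative variables in general, and the group comparison of complication-free survival is assigned to Cox and log-rank. Nor would a t-test on the observed days keep the 90%: with Weibull times at 9 vs 14 days and SD 7, its simulated power falls from 92% without early censoring to 53% with censoring of mean 15 days.

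Finally, a statistical analysis plan may hold more detail. The 90% claim and its basis are nevertheless fixed in the protocol, and that stated basis does not match the comparison the protocol itself plans.

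**Conclusion.** The point holds as a mismatch between the sizing and the analysis. The arithmetic for 84 is correct, and 102 follows from adding 20%. The 90% describes a comparison of mean days with no censoring; for the planned log-rank/Cox comparison it is unsupported, because no hazard ratio, event proportion or event count is given.

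The true power cannot be fixed from the protocol. In every exponential scenario with 84 patients it is below 90%, at best 84%. With SD 7 in each arm it ranges from well below 90% (long control times, heavy censoring) to above it (short control times, non-proportional hazards). The size therefore rests on the assumed control mean, the shape of the curves and the censoring pattern, all of which are assumptions here. The loss allowance is a minor side point. Severity: should-fix.

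**What to change.** Keep 102 patients and rewrite section 3.4 for the log-rank/Cox comparison:

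- State the assumed hazard ratio, or the two survival curves if hazards are not expected to be proportional.
- State the expected proportion of patients with a complication and the resulting number of events.
- Give the resulting power, or the hazard ratio detectable at 90%, over a range of event proportions.
- State that the present 90% applies only to a comparison of means of fully observed days.
- State that 102 covers a 17.6% loss, or that a 20% loss leaves about 82 evaluable patients and about 89% power on the means calculation.

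The cost is a recalculation and wording in one section. It needs no extra patients and no change to the analysis or data collection, but the stated power may turn out less favourable.
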